## Abstract

**Background:**

Postoperative pain control after total knee arthroplasty (TKA) remains a great challenge. The management of pain in the immediate postoperative period is one of the most critical aspects to allow speedier rehabilitation and reduce the risk of postoperative complications. Recently, periarticular infiltration anesthesia has become popular, but the outcome is controversial. Some studies have shown transient effects, “rebound pain”, or no effectiveness in pain control. Continuous intra-articular infusion technique has been introduced to improve these transient effects, but more clinical studies are needed. Furthermore, the potential risk of early periprosthetic joint infection is causing concerning. We plan to compare continuous intra-articular infusion anesthesia with epidural infusion anesthesia after TKA to assess the effectiveness of this technique in reducing pain, in improving postoperative function, and to look at the evidence for risk of early infection.

**Methods/design:**

This trial is a randomized, controlled study. Patients (*n* = 214) will be randomized into two groups: to receive continuous intra-articular infusion anesthesia (group C); and epidural infusion anesthesia (group E). For the first 3 postoperative days, pain at rest, active range of motion (A-ROM), rescue analgesia and side effects will be recorded. At 3-month and 6-month follow-up, A-ROM, C-reactive protein, erythrocyte sedimentation rate, and synovial fluid cell count and culture will be analyzed.

**Discussion:**

The results from this study will provide clinical evidence on the efficacy of a continuous intra-articular infusion technique in reducing pain, postoperative functional improvement and safety. It will be the first randomized controlled trial to investigate infection risk with local anesthesia after TKA.

**Trial registration:**

ClinicalTrials.gov identifier: ChiCTR-TRC-13003999

## Background

Pain after total knee arthroplasty (TKA) is usually severe. It causes a state of discomfort that may directly influence patients' functional recovery. The pain involved has specific characteristics: a 55 to 60% incidence at rest and up to70% upon mobilization; high or very high intensity; and pain peaking at 3 to 6 hours after surgery and continuing for the following 72 hours [1,2]. Anesthetic techniques such as epidural analgesia or peripheral nerve block may reach effective analgesic levels [3-5] in combination with opioid analgesics and non-steroidal anti-inflammatory drugs. Both techniques either have significant demands on technical skills, have potential side effects, or are costly [6-8]. Recently, local anesthesia techniques have become popular, including: (1) periarticular infiltration with or without local intermittent administration of anesthetics with an intra-articular catheter [6,7,9-12]; and (2) a combined technique with infiltration plus continuous infusion [8,13,14]. Local anesthesia has shown several advantages (less intensity of postoperative pain, less consumption of rescue analgesics and earlier discharge) when compared to other regional or purely systemic approaches [15-17].

There is some controversy surrounding periarticular infiltration anesthesia. Some studies, using single-dose or combined-dose periarticular infiltration, have shown transient effects, “rebound pain”, or no effectiveness in pain control [12,18-21]. The continuous intra-articular infusion technique has been introduced to improve these transient effects. Two previous studies [8,14] using continuous intra-articular infusion anesthesia showed better pain relief and less opioid use than a control group using saline infusion. Further investigation is needed to assess the efficacy of continuous intra-articular infusion anesthesia. One of the most concerning issues is whether continuous intra-articular infusion would increase the risk of early periprosthetic joint infection (PJI). Early diagnosis of PJI is challenging; at the present time, diagnosis of PJI remains dependent on clinical judgment and reliance on standard clinical tests including serologic tests, analysis of aspirated joint fluid, and interpretation of intraoperative tissue and fluid test results.

For this purpose, the aims of our study were: (1) to analyze the efficacy of continuous intra-articular infusion anesthesia in postoperative pain control and functional recovery compared with epidural analgesia; and (2) to investigate PJI markers, such as erythrocyte sedimentation rate (ESR), C-reactive protein (CRP), synovial fluid cell count and culture during follow-up, to determine whether the risk of early PJI increases with a continuous intra-articular infusion procedure.

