### Secondary outcome measures

#### **
*Periprosthetic joint infection markers*
**

Early diagnosis of PJI is challenging; at the present time, diagnosis of PJI remains dependent on clinical judgment and reliance on standard clinical tests including serologic tests, analysis of aspirated joint fluid, and interpretation of intraoperative tissue and fluid test results. During 3-month and 6-month follow-up, the CRP, ESR, synovial fluid culture, white blood cell (WBC) count and polymorphonuclear cell percentage (%PMN) will be measured.

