### Sample size

Calculation of sample size was based on two previous studies [20,25]. We assumed that postoperative pain during the 24- to 48-hour period will reach peak value and need effective pain control. Mean VAS scores over 24 to 48 hours for the two modes of analgesia were extracted. Group sample sizes of 93 for each group will achieve 80% power to detect a difference of 1.0 between the null hypothesis that both group means are 2.8 and the alternative hypothesis that the mean of group E is 1.8, with estimated group standard deviations of 3.1 and 1.4 and with a significance level (alpha) of 0.05 using a two-sided *t*-test. We plan to enroll a total of 214 participants with 107 in each group, allowing for a 15% withdrawal rate.

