### Data analysis

The statistical analysis will be performed using SPSS (Version 17.0) software (SPSS Inc., Shanghai, China). Normally distributed continuous variables will be compared using Student’s *t*-test. VAS and A-ROM will be analyzed with repeated measures for general linear models and multivariate analysis of variance. Data will be expressed as means (standard deviation), absolute numbers, and frequencies, when appropriate. *P* < 0.05 will be considered statistically significant for all comparisons.

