## Discussion

This study will provide clinical evidence on the efficacy of a continuous intra-articular infusion technique in reducing pain and improving postoperative function. In TKA, this remains a significant problem in the early postoperative period. Reduction of the patient's discomfort is the primary goal; reduction of the cost of narcotic use is a secondary goal. The epidural analgesia has been regarded as the gold standard in postoperative pain management, and it is associated with potential problems such as motor block, urinary retention and epidural bleeding (with anticoagulation therapy), and necessitates intensive observation of patients. The primary purpose of our study is to evaluate the efficacy of a continuous intra-articular infusion technique in relieving postoperative pain, reducing the need for postoperative narcotics, and improvement in postoperative function.

This study will be the first randomized controlled trial to investigate infection risk with a continuous intra-articular infusion technique after TKA. There has been concern about the risk of early PJI with periarticular multimodal drug injection and use of intra-articular catheters after TKA. Previous studies of local infiltration analgesia after unicompartmental knee arthroplasty or TKA have not found any increase in infection [7,15,20,26], but the evidence has been weak in most studies. At the present time, diagnosis of PJI remains dependent on clinical judgment and reliance on standard clinical tests including serologic tests and analysis of aspirated joint fluid. For this purpose, we will measure the ESR, CRP, synovial fluid cultures, WBC count, and %PMN at the 3-month and 6-month follow-up to identify early infections related to the surgical procedure.

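### Aim 2 promises to determine whether early joint-infection risk rises, but a trial sized only for pain cannot exclude a clinically important increase

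*Protocol article*

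**What the plan says.** The Background of the protocol article lists two aims. The second is to study infection markers "to determine whether the risk of early PJI increases with a continuous intra-articular infusion procedure". The Discussion repeats the ambition: "This study will be the first randomized controlled trial to investigate infection risk with a continuous intra-articular infusion technique after TKA".

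The infection measurements are secondary outcomes: "During 3-month and 6-month follow-up, the CRP, ESR, synovial fluid culture, white blood cell (WBC) count and polymorphonuclear cell percentage (%PMN) will be measured". The Discussion gives their purpose as finding early infections linked to the operation. The Safety section records side effects in the postoperative period. It names nausea, vomiting and constipation and adds a general category of other events, but does not name infection.

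The Sample size section rests on pain alone: "Mean VAS scores over 24 to 48 hours for the two modes of analgesia were extracted". It then states "Group sample sizes of 93 for each group will achieve 80% power to detect a difference of 1.0" and "We plan to enroll a total of 214 participants with 107 in each group, allowing for a 15% withdrawal rate". No PJI rate, power or margin is given. The Data analysis section has one general sentence that could cover the continuous markers, beginning "Normally distributed continuous variables will be compared using" and naming Student's t-test. It also provides for summaries as counts and frequencies.

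**The concern.** Early PJI is a rare yes/no event, and the aim is worded as a question the trial will settle. About 100 patients per arm is a sensible size for a pain score but very small for a rare event. If infusion doubled or even tripled the infection risk, the likeliest result would still be non-significant. Taken at its word, aim 2 would then be answered with no increase. The Discussion itself describes the earlier no-increase evidence as mostly weak, and this comparison would be open to the same criticism.

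A second, smaller matter is when infections are counted. The scheduled tests begin at 3 months. An infection that appears and is treated before then would enter the comparison only if it was recorded some other way.

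**Working it through.** **Inputs.** From Sample size: 93 evaluable and 107 enrolled per arm, difference 1.0, SDs 3.1 and 1.4, two-sided alpha 0.05, 80% power, 15% withdrawal. From Secondary outcome measures: infection tests at 3 and 6 months. The documents give no PJI base risk, so it is assumed to be 1%, 2% or 3%.

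**Step 1: the plan's own figure.** Average variance = (3.1² + 1.4²)/2 = (9.61 + 1.96)/2 = 5.785, so SD = 2.405. Then n = 2 × (1.96 + 0.84)² × 5.785 / 1.0², about 91 per arm. With the noncentral t it is 92, and power at 93 is 80.5%. The stated 93 reproduces, for pain. The enrolled 107 is 93 × 1.15. A 15% loss from 107 would leave 107 × 0.85 = 91, so 93 to 107 is, if anything, a slightly generous range for the infection comparison.

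**Step 2: power for PJI as a yes/no outcome.** For assumed risks p1 and p2, sum the binomial probabilities of all pairs of counts with a two-sided Fisher P of 0.05 or less in the direction of the increase. The last column uses n = [1.96 √(2p̄(1−p̄)) + 0.84 √(p1(1−p1) + p2(1−p2))]² / (p1−p2)², where p̄ is the mean of p1 and p2.

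| Assumed risks | Power, 93 per arm | Power, 107 per arm | n per arm for 80% power |
|---|---|---|---|
| 1% v 2% | 0.5% | 0.8% | 2,319 |
| 2% v 4% | 3.7% | 5.0% | 1,141 |
| 3% v 6% | 8.0% | 10.2% | 749 |
| 1% v 3% | 2.7% | 4.1% | 769 |
| 2% v 6% | 15.0% | 19.3% | 376 |
| 3% v 9% | 29.3% | 35.8% | 245 |
| 1% v 5% | 16.4% | 22.4% | 285 |

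From a 1% base, 80% power is reached when the other arm is at about 11% (93 per arm) or 10% (107 per arm).

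**Step 3: what it takes to reach P < 0.05.** With 93 per arm, 5 infections against none gives Fisher P = 0.059, and 6 against none gives 0.029. With 107 per arm, 6 against none is again the smallest such split.

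**Step 4: what a null result leaves open.** With no infections in an arm, the exact two-sided 95% upper limit is 1 − 0.025^(1/n): 3.9% for n = 93 and 3.4% for n = 107. The Newcombe 95% interval for the risk difference is about ±4.0 points (93) or ±3.5 points (107) for 0 v 0, and ±4.8 or ±4.2 points for 1 v 1. If the true risk were 1% in both arms, the chance of no PJI in the whole trial would be 0.99^186 = 15% or 0.99^214 = 12%.

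**Step 5: time window.** The aim concerns early PJI. The dedicated tests are at 3 and 6 months, and the only earlier capture described is the Safety section's general category. An infection before month 3 could be recorded there, but the text does not say that it will be counted towards the infection comparison.

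**The case against.** Several points on the other side are sound.

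- **Sizing on pain is normal practice.** The markers are secondary, and the Discussion puts pain, narcotic use and function first. This stands. The fault lies in how the aim is worded against the stated n, not in the choice of n.
- **A reader might infer that the plan compares only marker means.** The documents do not support this. The t-test sentence is general and does not mention the markers. Culture is categorical, counts and frequencies are provided for, and the Discussion describes case finding. A PJI definition may sit in a fuller document. None of this changes the result, because Step 2 already assumes a perfectly defined yes/no outcome.
- **The markers themselves can be compared.** At 80% power a standardised difference of (1.96 + 0.84) × √(2/93) = 0.41 is detectable, or 0.38 with 107 per arm. This also stands, but a shift in a marker is not a risk of infection, and risk is what the aim names.
- **A reader might infer that the design could never show an increase.** That is too strong, since an excess of about 10% to 11% against 1% would be detectable.
- **A reader might infer that infections before month 3 go unrecorded.** An overt one could be recorded as an adverse event, so incomplete counting is a possibility and not a certainty.
- **Nothing says a null will be reported as safety.** The Abstract speaks more modestly, of looking at the evidence. A misleading report is therefore a risk created by the aim's wording, not something the plan announces.

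**Conclusion.** The point holds in this limited form. Aim 2 claims more than a pain-sized trial can deliver on a rare event. Over assumed base risks of 1% to 3%, power for a doubling is about 0.5% to 10%, and for a tripling about 3% to 36%. At an assumed base of 0.5%, power for a doubling is under 0.1%, so the conclusion does not depend on the rate chosen within this range. A null result with 0 or 1 infection per arm would still be compatible with an absolute increase of about 3.5 to 4.8 points. The base rates are assumptions. The sample sizes and the wording of the aim come from the document, and no unseen case definition or choice of test would close the gap between them. The primary pain comparison is not affected.

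**What to change.** - Restate aim 2 as exploratory or descriptive, and bring the matching Abstract and Discussion statements into line.
- Make the infection outcome patient-level early PJI (yes/no) from surgery to 6 months. Build it from the tests already planned, plus any infection recorded as an adverse event, treated, or re-operated on since surgery.
- Report counts per arm and the risk difference with a 95% confidence interval.
- Treat between-arm comparisons of marker values as supportive.
- State that a null result will be interpreted by the upper confidence limit and not as absence of added risk.

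The cost is a weaker infection claim and one history item at visits that already take place. No extra patients, visits or invasive tests are needed.

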## Methods/design

### Study design

This is a randomized, controlled prospective study. The trial protocol has been approved by the Research Ethical Committee of Guangdong Provincial Hospital of Traditional Chinese Medicine (TCM) (reference, B2011-38-01). The trial will be conducted in accordance with the Helsinki Declaration, and will be monitored by the trial agency at Guangdong Provincial Hospital of TCM.

### Recruitment and consent

Patients scheduled for primary TKA at the Department of Orthopedic Surgery, Guang Dong Provincial Hospital of TCM, will be recruited, with a target sample size of 214 subjects. All candidates will go through a standardized interview process and receive more information about the study and the treatments. The participants’ written consents will be obtained. The purpose and procedures, and potential risks and benefits, of the study will also be explained thoroughly to the participants. Participants are able to withdraw from the study at any time without consequence. The trial will be executed from February 2014 to December 2015 including enrollment and follow-up (Figure 1).

**Figure 1 F1:**
[figure not shown]
Flow-chart of the study.

### Inclusion criteria

Participants meeting the following criteria will be included:

• Meet the diagnostic criteria for knee osteoarthritis;

• Planned spinal anesthesia; American Society of Anesthesiologists (ASA) physical status I-II;

• Scheduled for unilateral TKA;

• Patients aged 50 to 80 years old.

• Willingness to give written informed consent and willingness to participate in and comply with the study.

### Exclusion criteria

Participants meeting one or more of the following criteria will be excluded:

• Unwillingness of the patient;

• Presence of neuropathic pain or sensory disorders in the leg to be operated on;

• Intolerance to the study drugs;

• Failure of spinal anesthesia;

• Previous major knee surgery, re-operation or trauma to the knee within the study period.

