### Randomization and blinding

Random assignment was performed before surgery by using a computer generated, blocked random-allocation sequence with a 1:1 ratio. This study cannot be blinded because the different catheter placement is obvious.

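### The exclusion for re-operation or knee trauma within the study period, read naturally, removes randomised patients for events after treatment and can bias the 3- and 6-month infection and A-ROM comparisons

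*Protocol article*

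**What the plan says.** All references are to the protocol article.

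- **Exclusion criteria.** The list opens with "Participants meeting one or more of the following criteria will be excluded". It includes "Previous major knee surgery, re-operation or trauma to the knee within the study period" and "Failure of spinal anesthesia". No exception is made for patients already randomised or for re-operation because of infection.
- **Recruitment and consent.** "The trial will be executed from February 2014 to December 2015 including enrollment and follow-up".
- **Randomization and blinding.** "Random assignment was performed before surgery by using a computer generated, blocked random-allocation sequence with a 1:1 ratio". On blinding: "This study cannot be blinded because the different catheter placement is obvious".
- **Background, second aim.** The infection markers are studied "to determine whether the risk of early PJI increases with a continuous intra-articular infusion procedure".
- **Secondary outcome measures.** "During 3-month and 6-month follow-up, the CRP, ESR, synovial fluid culture, white blood cell (WBC) count and polymorphonuclear cell percentage (%PMN) will be measured".
- **Primary outcome measures.** A-ROM is listed as a primary outcome and is measured in the first 3 postoperative days and again at 3 and 6 months.

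**The concern.** Eligibility criteria should rest on facts known when the patient is randomised. A criterion that can be met during follow-up works as a rule for removing patients by outcome, and the groups left for comparison are no longer the groups that were randomised.

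Two features of this trial make that matter. First, one of the two aims is early PJI risk, and re-operation may be a consequence of infection. The Background and the Secondary outcome measures themselves count intraoperative tissue and fluid results among the means of diagnosing PJI, so the article links suspected infection with operating on the knee. A patient re-operated for infection before the 3-month visit could leave the trial before any protocol marker is taken. Second, re-operation and knee trauma plausibly go with poor function, so removal could flatter the late A-ROM results. Because allocation is known to everyone, a judgement about what counts as trauma can also be made with knowledge of the arm.

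At stake is false reassurance about the safety of the infusion, in a trial that presents itself as the first randomised one to examine this infection risk.

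**Working it through.** **Step 1: when can the criterion be met?** Patients are scheduled for primary TKA, and assignment precedes that operation. Earlier major knee surgery has its own words in the criterion. Re-operation within the study period therefore adds most if it means a further operation after the trial TKA, which is after randomisation. The study period includes follow-up, so later trauma is covered too.

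**Step 2: what could removal do to the infection comparison?** The article states no PJI rate, so the rates here are assumed: 1% in group E and 3% in group C. Let *p* be the true risk and *s* the share of infected patients removed because they were re-operated, taken as equal in both arms. The observed risk is *p*(1 − *s*)/(1 − *ps*).

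| *s* | Group C | Group E | Difference |
|---|---|---|---|
| 0 | 0.0300 | 0.0100 | 2.0 points |
| 0.5 | 0.015/0.985 = 0.0152 | 0.005/0.995 = 0.0050 | 1.0 point |
| 0.8 | 0.006/0.976 = 0.0061 | 0.002/0.992 = 0.0020 | 0.4 points |
| 1 | 0 | 0 | 0 |

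With 107 per group, these rates mean 107 × 0.03 = 3.2 and 107 × 0.01 = 1.1 expected cases, so each removal carries weight.

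**Step 3: which outcomes are touched?** VAS runs to 72 hours and rescue analgesia covers 3 days, so later re-operation or trauma has little bearing on them. The exposed outcomes are A-ROM and the infection markers at 3 and 6 months.

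**Step 4: spinal failure and power.** The plan's own figure comes first. With SDs of 3.1 and 1.4, the pooled SD is √((9.61 + 1.96)/2) = 2.405. For a difference of 1.0 the normal approximation gives 91 per group. The noncentral *t* gives power of 0.805 at 93 per group (0.803 with Welch degrees of freedom). The stated 93 for 80% power is reproduced.

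Now assume that spinal failure removes 1% to 5% of randomised patients, on top of the full 15% withdrawal:

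- 1%: 107 × 0.85 × 0.99 = 90.0 per group, power about 0.80
- 5%: 107 × 0.85 × 0.95 = 86.4 per group, power about 0.78

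The loss of power is small. All patients receive the same combined spinal-epidural block at L3-4, so failures should be roughly balanced between arms and little bias is expected.

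**The case against.** The strongest reply is that the wording is ambiguous and the harm inferred. The study period is given as calendar dates for the whole trial, so a patient enrolled in 2015 could have had knee trauma or an operation earlier within those dates. The word for prior surgery may also govern the whole phrase. The criterion does not mention infection, and it does not say whether exclusion is from the trial, from follow-up or from an analysis. The Safety section records adverse events separately, and nothing says that those records would be erased.

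Much of this stands, and it rules out several stronger readings that a reader might infer:

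- *The criterion can only be met after randomisation.* This is too absolute, given the calendar reading. The natural reading still includes later events, and no randomised patient is exempted.
- *The rule deletes the infections.* The documents support a risk of this. They give neither an infection rate nor the share of infected patients who would be re-operated.
- *Losing one or two cases would reverse the result.* With an assumed 3/107 versus 1/107, removing one group C case leaves 2 versus 1 and removing two leaves 1 versus 1. The difference shrinks or vanishes, and it does not reverse.
- *Spinal failure is a post-randomisation exclusion of the same weight.* Assignment before surgery does not settle whether it comes before or after the block, and the block is common to both arms.
- *The whole randomised comparison is broken.* The early pain outcomes, on which the sample size rests, are little affected.

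The article names no analysis set, but that may be left to a document not shown and is not part of this point. The point rests on a rule that the article does state.

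**Conclusion.** The concern holds for the re-operation and trauma clause. Set beside the definition of the trial period and the timing of assignment, the clause removes randomised patients for events after treatment. If it were followed and the infusion did raise infection risk, the infection comparison would be biased towards no difference. The late A-ROM comparison would lose patients likely to have poor function.

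The size cannot be fixed from the document. The fall from 2.0 points to about 1.0 point, or to zero, rests on assumed rates of 3% and 1% and on an equal share of infected patients removed in each arm. If the shares differed, which is possible in an open-label trial, the bias could be larger or smaller, or could run the other way. The harm is bias in the late outcomes. The spinal-failure criterion is a secondary matter of timing.

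**What to change.** 1. Limit the criterion to major knee surgery or knee trauma before randomisation, and delete the reference to events within the study period.
2. State that randomised patients with later re-operation or knee trauma stay in follow-up and in their allocated group.
3. Record every re-operation, with its reason, as a safety outcome, and count re-operation for infection as an infection outcome.
4. Apply the spinal-failure criterion only if failure is established before assignment. Otherwise keep those patients as well.

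The cost is a change of wording and one extra item on the case report form. The downside is that a few patients with later knee events stay in the analysis and add some variability to the late A-ROM and marker results.
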